## Abstract

**Introduction:**

Technological advances have enabled rapid screening for traumatic brain injury (TBI) at the point of care (POC), with devices approved by the United States Food and Drug Administration (FDA), in part to address throughput and resource allocation challenges in emergency departments (EDs). This point-of-care test quantifies the concentration of two biological markers of brain injury in whole blood after venipuncture.

**Methods:**

The objective of this study is to identify determinants for routine use of POC whole blood TBI test and to evaluate its impact on clinical and health system outcomes across three academic Level 1 trauma centers with accompanying EDs from three distinct geographical regions of the United States. We will utilize an effectiveness–implementation hybrid type II approach for this study involving 280 patients with Glasgow Coma Scale (GCS) scores of 13–15 (i.e., *“*mild*”* TBI).

**Results:**

Data will be collected (*n* = 140) using the POC whole blood TBI test, while simultaneously evaluating determinants of use to inform future widespread implementation efforts. An implementation blueprint will be developed and pilot tested at each site, while concurrently enrolling the final 140 patients with GCS 13–15.

**Discussion:**

Our goal is to provide evidence that use of the POC whole blood TBI test can reliably and safely improve clinical practice in EDs by reducing rates of unnecessary radiation exposure, shortening time spent in the emergency department, and demonstrating the efficacy of an implementation blueprint that can facilitate uptake of this test at similar Level 1 trauma center emergency departments.

**Clinical Trial Registration:**

[ClinicalTrials.gov], identifier [NCT07373509]

## Background

Approximately 5 million patients will be evaluated annually in United States emergency departments (EDs) for traumatic brain injury (TBI), and over 80% will undergo head computed tomography (CT) scans to identify potential intracranial pathology (1). Despite the high rate of head CT scans, <10% will be positive for intracranial pathology. Further, more than 90% of those evaluated will have a *“*mild” TBI [mTBI; categorized as Glasgow Coma Scale (GCS) 13–15], which is a type of brain injury associated with even lower rates of positive head CT scans (1). This clinical workflow results in millions of patients being unnecessarily exposed to radiation and increased ED visit costs. Overuse of CT scans in general contributes to ED overcrowding across the country (2). This issue is pervasive across both civilian and military EDs (3), resulting in negative impacts for individual and unit level readiness, particularly when resources are diverted away from additional emergency situations. There is also a significant financial impact due to these delays and overcrowding, as ED visits are more costly and resource-intensive than primary care appointments (4).

Technological advances have led to the development of rapid screening for TBI, approved by the United States Food and Drug Administration (FDA), in part to address throughput and resource allocation issues in EDs. The i-STAT Alinity TBI point-of-care test quantifies the concentration of two biological markers of brain injury in whole blood after venipuncture: glial fibrillary acidic protein (GFAP) and ubiquitin c-terminal hydrolase-L1 (UCH-L1) (5). GFAP is a filament protein found in astrocytes that provides structural support and stability to the central nervous system. UCH-L1 is an enzyme that recycles ubiquitin, an important regulatory protein. This test was FDA approved in 2024 as a Clinical Laboratory Improvement Amendment (CLIA) moderate complexity test for ruling out the need for a head CT scan when both biomarker values are below clinical cutoffs, achieving a nearly 100% negative predictive value (6). The test requires 15 min to deliver a result and does not require sample centrifugation to obtain plasma; instead, the test can be performed at the point of care (POC) using a small test cartridge and the Alinity iSTAT handheld reader.

### Preliminary work

In a preliminary study conducted at a Level 1 trauma center ED with 104 patients presenting with suspected mTBI (7), we found that the POC whole blood TBI test delivered results 2.5 h faster than a head CT scan (even when using the original plasma version of the test, which requires laboratory processing). As most EDs do not have a centrifuge, the use of plasma as the testing matrix requires transport of the sample to the central clinical laboratory for receipt, accessioning, centrifugation, and the delivery to the testing area. With the new POC whole blood TBI test, we anticipate additional time savings of 45 min due to not having to send the sample to the central laboratory. Emergency medicine physicians were surveyed about their decision to obtain head CT scans despite negative values for both biomarkers, indicating unfamiliarity with the POC whole blood TBI test, familiarity with the CT scan, and the perspective that the CT scans are more sensitive/specific. All patients received a head CT scan, regardless of the POC whole blood test result. Overall, nearly one in five patients could have avoided a head CT scan (due to a negative POC whole blood TBI test) in this sample (7).

### Current work

Despite receiving FDA clearance, recognition in national news campaigns, and electronic distribution of test information, ED providers do not routinely utilize this POC whole blood TBI test when evaluating patients with suspected mTBI or determining the need for CT scans. Others have identified additional barriers to routine use. These include entrenchment of CT scans as standard of care, narrow indication of clinical use (FDA approval limited to mTBI patients to rule out the need for a head CT scan), no recommendation yet in clinical guidelines, integration concerns with electronic health records, absence of a current procedural terminology code, and lack of education/awareness about the test and its cost-effectiveness (8–10). To address identified barriers, additional data on clinical effectiveness are needed to determine impact on patient and health system outcomes. In particular, there are no data to indicate other potential uses of the test to predict clinically relevant outcomes beyond ruling out head CT, such as ED length of stay and the incidence of return ED visits. In parallel, there is also an ongoing need to better understand contextual barriers to routine use among frontline clinicians. Therefore, the objective of this study is to identify determinants for routine use of the POC whole blood TBI test within ED settings and to evaluate impact on clinical and health system outcomes.

Each phase of the study will aim to do the following:
Phase 1: Evaluate determinants for routine use of the POC whole blood TBI test by assessing acceptability, adoption, appropriateness, and feasibility of the test at the organizational and provider level for each site and determine how these factors interplay with patient perspectives and knowledge to influence implementation of the test.Phase 2: Evaluate the effectiveness of the POC whole blood TBI test in determining the need for a head CT scan in approximately 140 patients with a Glasgow Coma Scale (GCS) scores of 13–15 in three Level 1 trauma center EDs (∼47 per site) while assessing secondary outcomes with clinical implications (i.e., reduction in ED length of stay and predictive utility for ED revisits for the same injury).Phase 3: Develop a site-specific implementation blueprint for use of the POC whole blood TBI test in determining the need for a head CT scan.Phase 4: Pilot test the implementation blueprint in approximately 140 patients with GCS scores of 13–15 in the ED (∼47 per site).

## Methods

Figure 1 illustrates the four phases of the study, including the goal, study population, and primary outcome measure. This study aims to enroll 280 patients with acute GCS scores of 13–15 across three sites (Phase 2 = 140, Phase 4 = 140). The three enrolling sites represent academic Level 1 trauma centers with accompanying EDs from three distinct geographical regions of the United States. Target enrollment for each site includes 47 acute ED patients in Phases 2 and 4.

**Figure 1 F1:**
[figure not shown]
Study protocol in phases.

### Patient participants

The study team will identify potential participants with suspected TBI according to approved local processes. Eligibility criteria may be reviewed through electronic medical records and patient interviews. Eligible patients may be approached to discuss participation. Enrolled patients will be asked to complete a brief battery of questionnaires about their injury and knowledge about concussion and radiation.

### Eligibility criteria

Inclusion criteria for patients are as follows: (1) age 18 or older, (2) presenting to an enrolling ED with arrival GCS 13–15 following reported blunt head impact, (3) presenting to the ED within 24 h of injury, and (4) meets Department of Defense definition of mTBI (a traumatically induced physiological disruption of brain function after external force, indicated by new onset or worsening of at least one of the following clinical signs: any alteration of mental status, any period of loss or decreased level of consciousness, or any loss of memory for events immediately before or after the injury). Exclusion criteria for patients are as follows: (1) treating ED provider does not determine need for a head CT, (2) inability to obtain results for POC whole blood TBI test within 24 h of injury, (3) preexisting neurologic condition, (4) contraindication or inability to complete blood draw, (5) significant polytrauma that, in the opinion of the principal investigators, could impact peripheral GFAP levels or require a full-body scan, (6) history of penetrating TBI, (7) history of neurosurgical intervention for previous TBI, (8) penetrating TBI for current injury, (9) any history of brain surgery, (10) any history of brain tumor, and (11) patients on psychiatric hold.

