
#### Phase 2

The goal of Phase 2 is to enroll approximately 140 patients across the three enrolling site EDs to establish current clinical practice patterns with regard to obtaining head CTs for patients who meet the study's inclusion/exclusion criteria. Prior to initiating patient enrollment, site principal investigators will brief emergency medicine and trauma faculty about the research study, the POC whole blood TBI test, and how to interpret the test results. The intent of this phase is to establish early stakeholder engagement and obtain feedback from frontline clinicians that will inform development of the implementation blueprint in Phase 4.

Timeline of participant outcome assessments can be viewed in Table 1. The primary endpoint of this phase is the rate of head CTs completed in enrolled patients. The secondary endpoint of this phase is the rate of head CTs completed in enrolled patients with negative POC whole blood test results. These primary and secondary endpoints were selected to match the FDA's framing of clinical benefit and to be directly comparable to ongoing and completed studies evaluating utility of blood biomarkers for CT utilization in the ED (6, 17–19). Additional secondary outcomes include ED length of stay (in minutes), return to ED for the same injury within 2 weeks of first ED presentation (yes/no), Military Acute Concussion Evaluation-2 (MACE-2) results, Neurobehavioral Symptom Inventory (NSI), and two customized surveys about knowledge of mTBI and knowledge of the effects of radiation exposure in healthcare settings. ED length of stay can be extracted from the electronic medical record by research personnel, as presentation and discharge from the ED are timestamped. The MACE-2 is a multimodal tool which assesses clinical signs of TBI, incident description, signs, symptoms, medical history, a brief cognitive exam, neurological exam, and modified Vestibular Ocular Motor Screening (VOMS). The MACE-2 takes approximately 15 min to complete. The NSI is a 22-item scale of TBI symptoms since the time of injury.

**Table 1 T1:** Timeline of patient participant outcome assessments.

Outcome	Enrollment	Two-week follow-up
Military Acute Concussion Evaluation—2	X	
Neurobehavioral Symptom Inventory	X	X
Traumatic brain injury knowledge	X	
Radiation exposure knowledge	X	
Quality of Life After Brain Injury Overall Scale		X
Follow-up care survey		X

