The goal of Phase 4 is to test the effect of the implementation blueprint on clinical practice patterns with regard to obtaining head CTs for patients who meet the study's inclusion/exclusion criteria across the three enrolling sites. Approximately 140 patients with presenting GCS scores between 13 and 15 will be enrolled across the three sites. The primary endpoint of Phase 4 (to be compared with the outcome of Phase 2) is the rate of head CTs completed in enrolled patients. The secondary endpoint of this phase is the rate of head CTs completed in enrolled patients with negative POC whole blood test results. We will also evaluate if the implementation blueprint has impacted baseline perceptions of facilitators and barriers and related implementation outcomes (i.e., adoption, appropriateness, acceptability, decisions, and feasibility) has shifted provider's perspectives on the test by having those who completed Phase 1 surveys (e.g., Mi-PARIHS) complete the surveys again.

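### Exclusion criterion 1 gates enrolment on the CT-need judgement that the blueprint is meant to change, without fixing it before the test result or requiring the CT to be outstanding

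*Protocol article*

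**What the plan says.** The first exclusion criterion in Eligibility criteria removes a patient when "1) treating ED provider does not determine need for a head CT". The second is "2) inability to obtain results for POC whole blood TBI test within 24 h of injury", which can be settled only once testing has been attempted. Neither criterion says when the CT judgement is made relative to the test result, and no criterion concerns a CT already performed.

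The Phase 4 section states that the primary endpoint, to be compared with Phase 2, "is the rate of head CTs completed in enrolled patients". It applies the same gate, since its goal concerns "obtaining head CTs for patients who meet the study's inclusion/exclusion criteria across the three enrolling sites".

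The Current work section describes the blueprint as being for "use of the POC whole blood TBI test in determining the need for a head CT scan". The Background gives the test's cleared purpose as "for ruling out the need for a head CT scan when both biomarker values are below clinical cutoffs".

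The Power analysis plans for CT rates of 95% in Phase 2 and 75% in Phase 4, with 140 patients per cohort, a two-tailed Fisher's exact test, alpha 0.01 and power 0.99.

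**The concern.** The judgement that admits a patient to the primary analysis is the one the intervention targets. The comparison is unrandomised and sequential, so nothing else in the design keeps the two cohorts alike on that judgement.

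Three things can follow from the literal wording.

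1. A Phase 4 provider who uses a negative result to conclude that no CT is needed has not determined a need. That patient, a success of the blueprint, would leave both numerator and denominator.
2. After the blueprint, providers may differ in whom they first judge to need a CT, so the cohorts may differ even if the judgement precedes the test.
3. A patient already scanned before the result is known meets every listed criterion and counts as a CT in either phase, whatever the test shows.

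The first and third shrink the observed reduction. The second could act in either direction. All three bear on the study's primary comparison. They cannot be repaired afterwards unless pre-test intention, CT timing and the exclusions have been recorded.

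**Working it through.** **Inputs from the article.** CT rates 95% (Phase 2) and 75% (Phase 4); n = 140 per cohort; two-sided Fisher's exact test; alpha 0.01 (all from Power analysis).

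**Inputs not in the article, taken as assumptions.** f is the share of no-CT patients removed by criterion 1. g is the share of each cohort enrolled after the CT was done. Both could lie anywhere from 0 to 1.

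**The plan's own figure.** Exact power, by full enumeration of both binomials, is 0.988 at 140 per cohort, against 0.99 stated. The smallest n reaching 0.99 is 145. The stated figure is reproduced for practical purposes.

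**Removal of no-CT patients.** If p is the CT rate with no removal, the observed rate is p / (1 − f(1 − p)).

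- Phase 4, f = 0.5: 0.75 / (1 − 0.5 × 0.25) = 0.75 / 0.875 = 85.7%.
- Phase 2, f = 0.5: 0.95 / (1 − 0.5 × 0.05) = 0.95 / 0.975 = 97.4%.

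| f | Phase 4 rate | Power, removal in Phase 4 only (Phase 2 stays 95%) | Phase 2 rate if also affected | Power, removal in both phases |
|---|---|---|---|---|
| 0 | 75.0% | 0.988 | 95.0% | 0.988 |
| 0.25 | 80.0% | 0.89 | 96.2% | 0.95 |
| 0.50 | 85.7% | 0.46 | 97.4% | 0.83 |
| 0.75 | 92.3% | 0.03 | 98.7% | 0.39 |

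At f = 0.5 the planned 20-point difference becomes 95.0 − 85.7 = 9.3 points (Phase 4 only) or 97.4 − 85.7 = 11.7 points (both phases). At f = 1 in both phases every enrolled patient has a CT and no effect can be seen.

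**Enrolment after CT.** If a share g of each cohort is already scanned and the rest follow the planned rates, the observed rate is g + (1 − g)p, and the difference shrinks by the factor (1 − g).

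- g = 0.25: 0.25 + 0.75 × 0.95 = 96.25%, against 0.25 + 0.75 × 0.75 = 81.25%. Difference 15 points, power 0.92.
- g = 0.50: 97.5% against 87.5%. Difference 10 points, power 0.69.

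**Dependence on alpha.** The Statistical analysis section sets 0.05 before Bonferroni correction. At 0.05 the f = 0.5 powers are 0.70 (Phase 4 only) and 0.94 (both phases).

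**The case against.** The strongest reply is that the article treats need and completion as different things. The planned 95% and 75% leave 5% and 25% of enrolled patients without a CT. The length-of-stay analysis compares test-negative patients who had only the test with those who also had a CT. Both require enrolled patients with a determined need and no CT. Patient participants has eligible patients approached after eligibility review, and the ethics section puts consent before study procedures, which suggests the order eligibility, consent, test. Restricting to patients for whom a CT is contemplated is also sensible for a rule-out test.

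This stands, and it defeats two stronger readings. A reader might infer that enrolment is conditioned on the primary outcome itself. It is not: the criterion concerns need, the endpoint completion. A reader might also infer that the Phase 2 rate misdescribes current practice by construction. Phase 2 does aim "to establish current clinical practice patterns with regard to obtaining head CTs", but that sentence goes on to limit the claim to patients who meet the study criteria.

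Nor do the documents support the idea that trained providers would declare a need merely to get low-risk patients tested. That is speculation.

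It may also be said that timing is detail an article leaves to the full protocol. That is only partly an answer. The criterion is given in full, and read literally it lets the intervention decide who is enrolled. The order of consent does not settle whether a Phase 4 test could be used clinically before enrolment, once the blueprint promotes its routine use.

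**Conclusion.** The point holds as a conditional weakness in how the gate is defined. If need is fixed before the result and is unaffected by the blueprint, and the CT is still outstanding at enrolment, the planned contrast is intact, with power 0.988. If not, the reduction is understated and the cohorts may not be comparable.

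The affected shares are not in the documents, so the powers above are a range under assumption, not an estimate. They take 95% and 75% as the rates that would be seen with no removal and no prior scanning. The after-CT figures further assume the same share in both phases, so that mechanism is dilution and not differential selection.

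It is worth correcting before enrolment starts, because the change is cheap and the information cannot be recovered later.

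**What to change.** - Reword criterion 1 as the treating provider's intention to obtain a head CT, recorded with a time stamp before any POC result is known and at the same step in Phases 2 and 4.
- Require that the head CT has not been performed at enrolment.
- Log criterion-1 exclusions by site and phase, and report the counts as a check on cohort comparability.
- State as a limitation, beside the seasonal, policy and staffing influences already named in the Discussion, that the blueprint may change who is first judged to need a CT. The rewording does not remove this.

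A sensitivity analysis that adds every criterion-1 exclusion as a no-CT patient is not advised. It would bring in people who were never CT candidates, impute outcomes for people not enrolled, and estimate a different quantity.

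Cost: an amendment to the eligibility criteria, one time-stamped case report form item and a screening-log tally. Recruitment may be slightly slower because patients already scanned can no longer be enrolled.

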### Funding and ethics approval

This study received the Health Sciences Research Award from the Congressionally Directed Medical Research Program's Traumatic Brain Injury and Psychological Health Research Portfolio (No. HT94252510275). The study received ethical approval from the University of Pittsburgh's Institutional Review Board on 24 November 2025 (No. STUDY25010137) in accordance with the Declaration of Helsinki. The study's protocol was registered on ClinicalTrials.gov on 4 February 2026 (No. NCT07373509) prior to the initiation of study procedures. All human subjects will provide informed consent prior to completing study procedures.

### Study design

We will utilize an effectiveness–implementation hybrid type II approach for this study involving 280 patients with GCS scores of 13–15 presenting to three civilian EDs (11). Study phases and progression are illustrated in Figure 1. In Phase 1, we will evaluate determinants for use to inform future widespread implementation efforts. In Phase 2, we will collect clinical effectiveness data using the whole blood TBI test. In Phase 3, we will develop an implementation blueprint for each site and disseminate to local stakeholders. In Phase 4, we will evaluate if clinical practice patterns change at each site in a separate cohort of 140 patients with GCS scores of 13–15.

### Whole blood TBI test

POC testing will be conducted using the iSTAT Alinity whole blood TBI cartridge and point-of-care analyzer (Abbott Laboratories, Chicago, IL, USA). The POC whole blood TBI test will be performed at each enrolling site within the FDA-approved indication and will be operated by appropriately trained personnel (6). Quality control and product validation will be performed according to manufacturer and CLIA requirements. A single venipuncture will be performed in the ED to obtain ∼3 mL of whole blood to be used for testing.

### Community advisory board

A diverse community advisory board (CAB) of stakeholders related to the implementation of the POC whole blood TBI test in the ED will be assembled to assist in Phases 3 and 4. The CAB will be assembled by the University of Pittsburgh's Clinical Translational Science Institute and will include representatives from each enrolling institution to provide site-specific context. Members of the CAB will include (from each site) recent acute mTBI patients in the ED, hospital administrators, ED physicians, ED staff (e.g., medical assistants), ED nurses, and the team's implementation scientist. The CAB will be assembled two times per year during the study period for a virtual meeting. Objectives of the initial meetings will be to brief the CAB on the final study design, outcomes (and what they mean), and objectives for conducting the study. Input from the CAB will be integrated into study procedures prior to the initiation of the study. Objectives of the subsequent meetings will be to brief the CAB on findings from Phases 1 and 2, and to discuss determinants (in their view) of successful implementation of the test.

#### Phase 1

The goal of Phase 1 is to establish determinants of use for the POC whole blood TBI test for each enrolling site's ED. To accomplish this goal, we will survey ED healthcare providers to identify determinants of routine use, decision-making processes, and perspectives on acceptability, appropriateness, adoption, and fidelity.

To evaluate determinants of routine use, the Mobilizing Implementation of iPARIHS Facilitation Planning tool (Mi-PARIHS) will be administered as the primary outcome measure for this phase. The Mi-PARIHS is a 34-item tool which supports users in their assessment of the innovation, context and recipient constructs, development of a tailored facilitation plan, and repeated use over time to evaluate the effectiveness of facilitation strategies. Each question is rated on a five-item Likert scale to identify barriers and facilitators/enablers for the innovation being evaluated, where −2 indicates a barrier and +2 indicates a facilitator for that aspect of implementation. In alignment with the i-PARIHS framework, domain scores are summed across innovation, recipients, and context items where higher scores indicate more facilitators/enablers and lower scores indicate more barriers.

The Decisional Conflict Scale (DCS) will be used to assess factors influencing the decision-making processes of providers when deciding between use of the POC whole blood TBI test and CT scanning (12). The DCS measures five dimensions of decision-making, evaluating uncertainty, lack of information, unclear values, lack of support, or ineffective decision-making. The acceptability of intervention measure (AIM) (13) is a five-item measure evaluating the perception among implementation stakeholders that a given practice is agreeable or satisfactory. This tool will assess providers’ perspectives on how acceptable the POC whole blood TBI test is for assessing need for CT and determining the plan of care for patients presenting with mTBI. The AIM has excellent structural and known-groups validity as well as test–retest reliability [intraclass correlation coefficient (ICC) = 0.82] (13). The Intervention Appropriateness Measure (IAM) will also be administered to assess baseline perceptions of the appropriateness of the POC whole blood TBI test (13). The IAM is a five-item measure evaluating the perceived relevance of the test for a given setting. The IAM has excellent structural and known-groups validity as well as test–retest reliability (ICC = 0.94) (13). Adoption will be evaluated by the Adoption of Information Technology Innovation (AITI) (14), a 25-item instrument designed to study adoption of new technologies. The scale has excellent reliability and validity metrics (15). The Williams Intention to Adopt Measure (WIAM) will also be used to evaluate adoption (16). The WIAM will be adapted to the current study to understand the willingness of ED providers to adopt the POC whole blood TBI test. This is a five-item measure where the provider will answer if they have spoken with colleagues about experiences with the POC whole blood TBI test; whether they intend to use the POC whole blood TBI test at each visit; whether they have attended trainings, workshops, or other learning sessions focused on the POC whole blood TBI test; and whether they have searched the literature about point-of-care blood tests for TBI for use with patients. The provider will be asked to rate their intended use of the POC whole blood TBI test across the next 10 patients seen in the ED. The WIAM uses a seven-point scale, ranging from 1 (strongly disagree) to 7 (strongly agree), except for the final question, which ranges from 0 to 10. The WIAM has some of the best psychometric properties among adoption measures (16). Lastly, feasibility will be assessed at baseline using the Feasibility of Intervention Measure (FIM) (13). The FIM is a five-item measure which evaluates the extent to which an assessment can be successfully carried out within a given clinical setting. The FIM has excellent structural and known-groups validity, as well as test–retest reliability (ICC = 0.87) (13).

#### Phase 2

The goal of Phase 2 is to enroll approximately 140 patients across the three enrolling site EDs to establish current clinical practice patterns with regard to obtaining head CTs for patients who meet the study's inclusion/exclusion criteria. Prior to initiating patient enrollment, site principal investigators will brief emergency medicine and trauma faculty about the research study, the POC whole blood TBI test, and how to interpret the test results. The intent of this phase is to establish early stakeholder engagement and obtain feedback from frontline clinicians that will inform development of the implementation blueprint in Phase 4.

Timeline of participant outcome assessments can be viewed in Table 1. The primary endpoint of this phase is the rate of head CTs completed in enrolled patients. The secondary endpoint of this phase is the rate of head CTs completed in enrolled patients with negative POC whole blood test results. These primary and secondary endpoints were selected to match the FDA's framing of clinical benefit and to be directly comparable to ongoing and completed studies evaluating utility of blood biomarkers for CT utilization in the ED (6, 17–19). Additional secondary outcomes include ED length of stay (in minutes), return to ED for the same injury within 2 weeks of first ED presentation (yes/no), Military Acute Concussion Evaluation-2 (MACE-2) results, Neurobehavioral Symptom Inventory (NSI), and two customized surveys about knowledge of mTBI and knowledge of the effects of radiation exposure in healthcare settings. ED length of stay can be extracted from the electronic medical record by research personnel, as presentation and discharge from the ED are timestamped. The MACE-2 is a multimodal tool which assesses clinical signs of TBI, incident description, signs, symptoms, medical history, a brief cognitive exam, neurological exam, and modified Vestibular Ocular Motor Screening (VOMS). The MACE-2 takes approximately 15 min to complete. The NSI is a 22-item scale of TBI symptoms since the time of injury.

**Table 1 T1:** Timeline of patient participant outcome assessments.

Outcome	Enrollment	Two-week follow-up
Military Acute Concussion Evaluation—2	X	
Neurobehavioral Symptom Inventory	X	X
Traumatic brain injury knowledge	X	
Radiation exposure knowledge	X	
Quality of Life After Brain Injury Overall Scale		X
Follow-up care survey		X

Patients will also receive a series of surveys to complete remotely approximately 2 weeks after the initial visit. Patients will complete the NSI, the Quality of Life After Brain Injury Overall Scale (QOLIBRI-OS), and a brief custom survey about follow-up clinical care. The QOLIBRI-OS is a 6-item tool evaluating how a participant's brain injury has impacted their health-related quality of life.

#### Phase 3

The goal of Phase 3 is to design and deploy site-specific implementation blueprints based on determinants of use identified in Phase 1 and stakeholder feedback and practice patterns from Phase 2. The i-PARIHS framework will be used to select implementation strategies that will address identified facilitators and barriers from the Mi-PARIHS assessment in Phase 1.

